### Molecular profiling analysis

Somatic mutations in genes reported to be associated with myeloid pathology potentially linked to the pathogenesis or clinical behavior of autoimmune cytopenias will be analyzed. Whole exome sequencing (WES) will be performed, focusing first on genes involved in proliferation/apoptosis pathways (RAS, TP53), DNA methylation (IDH1/IDH2, DNMT3A, TET2, ASXL1), and RNA splicing (SF3B1, NOTCH), and then extended to possible pathogenic variants. WES analysis will be based on a target enrichment system for next generation sequencing (NGS), allowing efficient, simple, and rapid analysis of genomic regions of interest in a large number of samples. For NGS, 50 ng of non-amplified genomic DNA from peripheral blood mononuclear cells will be enriched for target exons by liquid-

[figure not shown][figure not shown]

Dipartimento di Medicina Interna  
UOC EMATOLOGIA  
Pad. Marcora / Granelli  
Direzione [contact]  
Amb: [name] - DH: [name]  
Reparti: CTMO [name] - AOE [name]  
Mail: [contact]

- Direttore: [name]

phase hybridization using a SureSelect custom kit designed to capture all coding exons ( $n = 2,045$ ) of 104 target genes (Agilent Technologies), according to an optimized automated processing protocol. After attaching index sequences to discriminate respective samples, the enriched target DNA will undergo massive parallel sequencing using a NextSeq 550 sequencer (Illumina) with a default protocol of 150 bp paired-end reads. Sequencing results will be analyzed through our pipeline to identify somatic mutations. All sequencing reads will be aligned to the human reference genome (hg19) using BWA version 0.5.8 with standard parameters. After removing duplicate or low-quality reads, allele frequencies of single nucleotide variants (SNVs) and indels at each genomic position will be calculated by enumerating relevant reads using samtools. Variants with allele frequency  $>2\%$  and supported by  $>5$  reads will be extracted and annotated using ANNOVAR28. Synonymous and ambiguous variants will be discarded.

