Missense SNVs already present in public and private single nucleotide polymorphism (SNP) databases and missense SNVs with allele frequency between 0.45 and 0.55 will be filtered as polymorphisms. Among missense SNVs with allele frequency 0.45–0.55, known hotspot mutations will be considered somatic mutations. The significance of observed mutations in each gene will be assessed by calculating the type I error under the null hypothesis that all observed non-silent mutations are "passenger changes," assuming a Poisson distribution with a uniform background mutation rate ( $\lambda$ ).

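### Both germline filters cover only missense SNVs, so other germline variants pass as somatic; the fixed 0.45–0.55 window has no stated read depth behind it

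*Protocol*

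**What the plan says.** All of the following is in the Protocol, section 7.2, under Molecular profiling analysis, unless another section is named.

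- **Source.** The input is "50 ng of non-amplified genomic DNA from peripheral blood mononuclear cells". No matched non-blood sample is named for subtracting germline variants.
- **Calling.** Allele frequencies are computed for SNVs and indels. Variants above 2% and supported by more than 5 reads are kept, and no upper frequency limit is set. Then "Synonymous and ambiguous variants will be discarded"; what makes a variant ambiguous is not defined.
- **Germline filters.** The first removes "Missense SNVs already present in public and private single nucleotide polymorphism (SNP) databases". The second says that "missense SNVs with allele frequency between 0.45 and 0.55 will be filtered as polymorphisms". One exception is made among missense SNVs inside that window: "known hotspot mutations will be considered somatic mutations".
- **Use.** Each gene is tested against the null that all its observed non-silent mutations are passengers, "assuming a Poisson distribution with a uniform background mutation rate". Section 2.2 also plans a preliminary correlation of somatic mutations with response, relapse and complications.
- **Assay.** The text says "Whole exome sequencing (WES) will be performed, focusing first on genes involved in proliferation/apoptosis pathways", but the reagent is a "SureSelect custom kit designed to capture all coding exons" of 104 genes. Section 1.1 speaks of targeted sequencing.

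**The concern.** With no matched germline sample, the list of somatic mutations is only as good as the filters. Both filters are written for one variant class, while the calling step and the gene-level test cover more. A germline frameshift or stop-gain variant therefore passes through to a list labelled somatic.

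Within the missense class, a fixed window of plus or minus 0.05 ignores the fact that the spread of an observed allele frequency depends on read depth. The protocol states no depth, so nothing in the text keeps the rule in a range where it works.

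Patients wrongly labelled as mutated would dilute real associations with response or relapse. Germline variants would add to the counts in the Poisson test. Section 7.1 expects only 40–50 relapses, which leaves little information to absorb a misclassified exposure.

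**Working it through.** **Context figures from the plan.** The protocol gives no error rate for the filter, so none can be reproduced. Its sample size does reproduce: (40 + 40 + 20) × 2 = 200 patients. So does its relapse count: 0.30 × (40 + 40) × 2 = 48, within the stated 40–50.

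**Step 1: which germline variants each stated filter covers.**

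| Germline variant | Database filter | 0.45–0.55 window |
|---|---|---|
| Missense, listed in a database | removed | not needed |
| Missense, unlisted, heterozygous | no | depends on depth (step 2) |
| Missense, unlisted, homozygous (near 1.0) | no | no |
| Nonsense, splice, indel, listed or not | no | no |

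The last two rows do not depend on depth. Only the undefined ambiguous category could remove such variants.

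**Step 2: leak through the window for unlisted heterozygous missense variants.** Let X be the number of variant reads at depth d, with X ~ Binomial(d, 0.5). The leak is 1 − P(0.45d ≤ X ≤ 0.55d). At d = 100 the window holds 45 to 55 reads, and the leak is 0.271. Depth is an assumption throughout. The last two columns are sensitivity runs, also on assumed values: a mean of 0.48 for reference bias, and beta-binomial overdispersion of 0.005.

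| Reads | Ideal binomial | Mean 0.48 | Overdispersion 0.005 |
|---|---|---|---|
| 50 | 48.0% | 49.7% | 52.8% |
| 100 | 27.1% | 30.9% | 37.0% |
| 200 | 13.7% | 19.9% | 29.4% |
| 300 | 7.3% | 14.3% | 25.8% |
| 500 | 2.2% | 8.3% | 22.3% |
| 1000 | 0.1% | 2.7% | 19.3% |

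**Step 3: what that could mean in 200 patients.** The number of unlisted heterozygous missense variants per patient is not in the protocol. Assume 0.5 to 1. False somatic calls = 200 × (0.5 to 1) × leak. Under ideal sampling this gives about 27 to 54 at 100 reads, 14 to 27 at 200, and 2 to 4 at 500.

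**Step 4: error in the other direction.** A true somatic non-hotspot missense variant at frequency 0.48 falls inside the window, and is discarded, 69% of the time at 100 reads and 92% at 500.

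**Step 5: hotspots.** The exception applies only inside the window. A known hotspot that also appears in a SNP database is kept at frequency 0.50 and removed at 0.10.

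**Step 6: calling limit.** More than 5 reads means at least 6. Since 6 / 0.02 = 300, the 2% limit governs only from about 300 reads. At 100 reads the effective floor is 6 / 100 = 6%.

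**The case against.** The strongest reply is that the window is only the second line of defence. The database filter removes listed missense variants at any allele frequency, including homozygous ones. That stands. The percentages in step 2 are therefore not shares of all germline variants. They apply only to unlisted heterozygous missense variants, whose number the protocol does not give. A reader might infer that the window cannot separate germline from somatic at all, or that it carries the whole task; the text does not support either reading.

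Depth is also assumed. The 2% calling limit has a function only from about 300 reads, which hints at deep sequencing. There the ideal leak is 7% or less. This is fair, but it is an inference: no minimum depth is written down, and modest bias or overdispersion raises the figures.

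Three further inferences should be resisted.

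- Multiplying 104 genes by a 5% level to predict false-positive genes uses a level that the protocol does not state.
- Discarding synonymous variants from the candidate list does not show that they are unavailable for estimating the background rate.
- The planned extension is to possibly pathogenic variants. It can be read as lying within the 104 genes, so it is not shown to be impossible. The whole-exome label is a misdescription and no more than that.

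Finally, the Statistical analysis text in section 7 names only cytokines and microbiota for correlation with outcome. The link from mutations to outcome rests on section 2.2, which calls it preliminary.

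None of this answers the restriction to missense SNVs. That is a stated rule, not a detail left to an analysis plan.

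**Conclusion.** The point holds in a limited form. The firm part needs no assumption about depth: as written, germline nonsense, splice and indel variants, and unlisted homozygous missense variants, face no stated germline filter except the undefined removal of ambiguous variants. They enter the non-silent Poisson test and the section 2.2 correlation as somatic. How many there would be cannot be derived from the protocol.

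The conditional part is the window's leak for unlisted heterozygous missense variants. Under ideal binomial sampling it is substantial at 200 reads or fewer (14% at 200) and negligible at 1000 (0.1%). The rule for hotspots is inconsistent at any depth.

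This affects a secondary, preliminary analysis. The primary endpoint, the number of laboratory tests needed to reach a diagnosis (section 5.1), is untouched. The change should be made, but the study does not stand or fall by it.

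**What to change.** In section 7.2, Molecular profiling analysis:

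1. Apply the germline filters to every non-silent class, including nonsense, splice and indel variants, and define what is discarded as ambiguous.
2. Replace the fixed window with a depth-based test: a variant is germline-compatible if its read counts fit 0.5 or 1.0 under a binomial model that allows overdispersion. State the minimum depth at which the test is used.
3. Filter on a stated population-frequency cut-off instead of mere presence in a database.
4. Keep known hotspots at any allele frequency, whether or not a database lists them.
5. Report the remaining germline-compatible non-hotspot variants as of uncertain origin. Leave them out of the main somatic count and include them in a sensitivity analysis.
6. Describe the assay as a 104-gene panel in place of whole exome sequencing.

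The cost is bioinformatics work and wording, with no new samples. The drawback is that some true somatic variants at high allele frequency move to the uncertain group, and more of them do so at low depth, where the germline-compatible zone is wider. The sensitivity analysis shows how much this matters.

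### The per-gene passenger-mutation test assumes one uniform Poisson background rate, so genes without a driver are called significant when passenger rates differ between genes

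*Protocol*

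**What the plan says.** Section 7.2, Molecular profiling analysis, sets out the assay, the variant filters and then a test.

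- **Genes.** The analysis covers "genes reported to be associated with myeloid pathology". The text says "Whole exome sequencing (WES) will be performed", but the capture step it describes is a "custom kit designed to capture all coding exons" "of 104 target genes (Agilent Technologies").
- **Filters.** Variants must pass an allele-frequency threshold (above 2%) and a read threshold (more than 5 reads). After annotation, "Synonymous and ambiguous variants will be discarded". Missense variants found in SNP databases, or with allele frequency 0.45-0.55, are then removed as polymorphisms, except known hotspots.
- **Test.** "The significance of observed mutations in each gene will be assessed by calculating the type I error" under the null that all of the gene's non-silent mutations are passengers, "assuming a Poisson distribution with a uniform background mutation rate".

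The protocol does not say where the rate comes from, whether it is per gene or per base, or what threshold applies. Those details may be left to an analysis plan. The uniform rate is not left open: it is fixed here.

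**The concern.** The hypothesis of interest for a gene is that its mutations are all passengers. The reference distribution adds a second condition, that every gene has the same background rate. A small p-value can therefore mean that the gene carries a driver, or only that its passenger rate is above average. If the rate is per gene and not per base, it can also mean only that the gene is long. This happens whether the rate is estimated in the study or taken from outside.

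Synonymous variants are the natural in-study measure of neutral mutation, and the filters remove them before the test is described. If the rate were then pooled from the non-silent counts of a panel chosen for myeloid relevance, real drivers would inflate the background they are judged against.

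At stake is whether a per-gene significance call can be read as evidence of a driver.

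**Working it through.** The protocol states no rate, expected count, threshold or power for this test, so there is no figure of its own to reproduce.

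**Inputs from the protocol:** 104 target genes; at least 200 patients (section 7.1); Poisson null with one rate λ.

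**Assumed, because the protocol gives none:** total mutations 50 to 400; coefficient of variation (CV) of passenger rates between genes 0 to 1.0 (gamma); spread of coding length (log-normal SD 0.8); driver prevalences; Bonferroni as a yardstick, 0.05/104 = 0.00048.

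**Test:** p = P(X ≥ x | Poisson(λ)), upper tail.

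**1. One gene by hand.** With λ = 5, the smallest count with p ≤ 0.05 is 10, since P(X ≥ 10 | 5) = 0.032. A passenger-only gene whose true mean is 10, twice the average, reaches that count with probability P(X ≥ 10 | 10) = 0.54.

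**2. Per-gene false-positive rate, no drivers, nominal 0.05** (negative binomial counts against the Poisson critical value):

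| Mean count per gene | CV 0 | CV 0.5 | CV 1.0 |
|---|---|---|---|
| 1 | 0.019 | 0.033 | 0.063 |
| 5 | 0.032 | 0.100 | 0.162 |
| 10 | 0.049 | 0.164 | 0.218 |

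At mean count 5 the expected number of false genes is 104 × 0.032 = 3.3, 104 × 0.100 = 10.4 and 104 × 0.162 = 16.8.

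**3. Chance of at least one false Bonferroni-significant gene among 104, no drivers** (simulation, λ = panel mean):

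| Total mutations (mean per gene) | Equal rates | CV 0.5 | CV 1.0 | Equal per-base rates, length ignored |
|---|---|---|---|---|
| 50 (50/104 = 0.48) | 0.02 | 0.06 | 0.32 | 0.31 |
| 100 (0.96) | 0.02 | 0.13 | 0.65 | 0.63 |
| 200 (1.92) | 0.02 | 0.30 | 0.94 | 0.91 |
| 400 (3.85) | 0.03 | 0.64 | 1.00 | 1.00 |

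The last column applies only if λ is a per-gene rate.

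**4. Power, only if λ is pooled from the panel's non-silent counts.** The target gene is mutated in 3% of 200 patients (expected 6), background is 0.5% (expected 1 per gene), and alpha is 0.05. With the true background, λ = 1, the critical count is 4 and power is P(Bin(200, 0.03) ≥ 4) = 0.85. With 20 other driver genes and 83 background genes, the pooled mean is 200 × (83 × 0.005 + 0.03 + 20 × prevalence)/104:

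| Prevalence of the 20 other drivers | Pooled λ | Power |
|---|---|---|
| 2% | 1.63 | about 0.73 |
| 3% | 2.01 | about 0.62 |
| 10% | 4.70 | about 0.12 |

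With 5 or 10 other drivers, power is about 0.83 and 0.74 at 3% prevalence, and about 0.66 and 0.41 at 10%. With an external or neutral λ it stays at about 0.85 throughout.

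**The case against.** Four arguments carry weight on the other side.

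- **Sparse counts protect the test.** At a mean of one mutation per gene, the discrete Poisson test holds its nominal 0.05 up to a CV of 0.75 (0.048) and reaches only 0.063 at CV 1. The any-gene figures also build up from small per-gene errors: 13% at 100 mutations and CV 0.5 is roughly 0.1 false genes expected. This stands as a limit on size. Even so, the rate at CV 1 is about three times the equal-rate value of 0.019, and inflation grows as mutations accumulate.
- **Power loss is not built into the test.** A reader might infer that, with synonymous variants gone, the rate can come only from the counts under test. The text does not say so. The rate could be external, could use other genes if whole-exome data exist, or could use synonymous variants counted before removal. The severe losses also need 10 to 20 other genes each mutated in 10% of patients; 20 such genes means 20 × 0.10 = 2 driver mutations per patient on average. The power loss is therefore conditional.
- **Length may not be ignored.** The protocol does not exclude a per-base rate, so the length-ignored column is also conditional.
- **No downstream damage is shown.** A reader might infer that an unreliable list of significant genes feeds the outcome correlations. Section 2.2 correlates the mutations identified, not genes that pass this test, and the Statistical analysis section correlates cytokines and microbiota. That inference fails.

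The objections leave untouched that the uniform rate is an explicit choice and that it over-rejects when gene rates differ.

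**Conclusion.** The concern holds as a fault in the stated null model. With one background rate for all genes, a significant result does not separate a driver from a high passenger rate. At a CV of 0.5 to 1.0, at least one false Bonferroni-significant gene is expected with probability about 6-32% at 50 mutations, 13-65% at 100 and 30-94% at 200, against about 2% with equal rates. If the rate is per gene and length is ignored, the chance is about 31-91% over the same totals even with equal per-base rates. All of this rests on assumed counts and spreads.

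Loss of power is a second, conditional risk. It arises only if the rate is pooled from this panel's non-silent counts, is modest when other drivers are at 2-3% prevalence (0.85 to about 0.62-0.73 with 20 of them), and is severe only when many are at 10%.

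The effect is confined to the per-gene significance calls of an exploratory analysis. The primary endpoint, the listed secondary endpoints and the sample size are unaffected. The correction is worth making because it is cheap, not because the study depends on it.

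**What to change.** In Molecular profiling analysis:

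1. Replace the uniform rate with a gene-specific expected count: covered coding length times a neutral background rate. State the source and unit of that rate.
2. Allow over-dispersion between genes, for example with a negative binomial model or a non-synonymous to synonymous ratio test.
3. Control the false-discovery rate over the genes tested. State whether these are the 104 panel genes or the exome, since the section describes both.
4. Keep synonymous variants for background calibration only, and drop them from the candidate list. Apply to them the same read and allele-frequency thresholds and the same SNP-database and 0.45-0.55 germline filters used for missense variants. At present those germline filters are written for missense variants alone and no matched germline sample is described, so unfiltered synonymous calls could include inherited polymorphisms and inflate the background. Alternatively, use a stated external neutral rate.

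The cost is pipeline and wording changes; no new samples or sequencing are needed. The drawback is statistical: with few synonymous variants the background is imprecise, and fewer genes will reach significance.

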### **Microbiota analysis**

For each enrolled case, a nasopharyngeal swab and a fecal sample will be collected at enrollment and at any relapse, prior to the administration of any new line of therapy. Respiratory/fecal samples collected will undergo bacterial genomic DNA extraction and amplification of the hypervariable V1–V3 region of the 16S rRNA gene. Library preparation and subsequent sequencing using the MiSeq Illumina method will enable precise characterization of the resident flora, at least at the bacterial genus level. Data will be analyzed with appropriate statistical methods to evaluate potential differences in nasal/fecal microbiota composition during follow-up and in relation to different therapies administered.

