## 4. STUDY PROCEDURES

### 4.1 Intervention

Enrollment:

- Venous blood draw for somatic DNA mutation and cytokine profile studies
- Nasopharyngeal swab and fecal sample for microbiota analysis
- Medical history, physical exam, anthropometrics
- Blood, urine, and instrumental tests as clinically indicated to assess hematologic disease status
- For the marrow substudy, samples will be used to study immunological microenvironment, cytokine patterns, and RBC metabolism.

Follow-up (every 1–3 months for AIHA and ITP, every 6–12 months for CIN, according to clinical need):

- Blood for cytokine profiling
- Nasopharyngeal swab and fecal sample for microbiota analysis

[figure not shown][figure not shown]

Dipartimento di Medicina Interna  
UOC EMATOLOGIA  
Pad. Marcora / Granelli  
Direzione [contact]  
Amb: [name] - DH: [name]  
Reparti: CTMO [name] - AOE [name]  
Mail: [contact]

- Direttore: [name]

- Medical history, physical exam, anthropometrics
- Blood, urine, instrumental tests as indicated

At relapse:

- Blood/marrow, nasopharyngeal swab, fecal sample, clinical evaluation, and lab tests as above. Samples stored at the Hematology and Transfusion Medicine Laboratory biobank.

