## **10. STUDY MANAGEMENT**

### **10.1 Data collection and management**

A responsible referent will be identified for procedures of data collection, quality verification, and transmission. Collected information will be entered by trained personnel into a dedicated database. At study registration and during scheduled periodic control visits (according to standard clinical practice) or disease progression, specified clinical information and samples of peripheral blood for molecular and cytokine studies, fecal samples, and nasopharyngeal swabs for microbiome studies must be collected.

Registration will be done in a limited-access database: the physician will complete the registration form after obtaining dated and signed informed consent from the patient. Patients will be assigned a progressive three-digit identification code starting from 001 based on enrollment order.

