#### **10.2.3 Informed Consent (IC)**

The investigator or designated personnel must inform subjects about all aspects and procedures of the study.

The informed consent process must comply with applicable regulatory procedures. The investigator (or designated collaborator) and the subject must date and sign the consent form before any study-related procedures. Subjects receive a copy of the signed IC; the original is kept in designated study archives. Neither investigator nor staff may coerce or unduly influence subjects to participate or continue in the study. Participation must be voluntary, and subjects must be informed they may withdraw consent at any time without penalty or loss of benefits.

Written or oral study information, including consent forms, must not contain language that waives

[figure not shown][figure not shown]

Dipartimento di Medicina Interna  
UOC EMATOLOGIA  
Pad. Marcora / Granelli  
Direzione [contact]  
Amb: [name] - DH: [name]  
Reparti: CTMO [name] - AOE [name]  
Mail: [contact]

- Direttore: [name]

subjects' legal rights or releases investigators or sponsors from liability for negligence.

Patients meeting inclusion criteria will be invited to provide peripheral blood samples for cytokine profiling during scheduled visits and symptom-driven visits, and consent to use of their personal and clinical data for research. Nasopharyngeal swabs and fecal samples will be collected at enrollment and at 1, 3, 6, and 12 months for microbiota complexity studies.

Patients will have adequate time to read the information and ask questions.

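### Sections 4.1, 7.2 and 10.2.3 set three different microbiota sampling schedules, and 7.2 followed as written gives no follow-up sample in patients who do not relapse

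*Protocol*

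**What the plan says.** Four places in the protocol say when the swab and stool sample are taken.

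- **Section 4.1 (Intervention).** The item "Nasopharyngeal swab and fecal sample for microbiota analysis" is listed at enrolment and again at follow-up, where visits run "every 1–3 months for AIHA and ITP, every 6–12 months for CIN, according to clinical need". Both specimens are listed again at relapse.
- **Section 7.2 (Microbiota analysis).** Here the rule is that "a nasopharyngeal swab and a fecal sample will be collected at enrollment and at any relapse". The same sentence adds that sampling comes before a new treatment line is started. No scheduled follow-up sample is mentioned.
- **Section 10.2.3 (Informed Consent).** "Nasopharyngeal swabs and fecal samples will be collected at enrollment and at 1, 3, 6, and 12 months for microbiota complexity studies". There is no exception for CIN, no relapse sample, and nothing after month 12.
- **Section 10.1 (Data collection and management).** Samples are required at registration and "during scheduled periodic control visits (according to standard clinical practice) or disease progression", which is in line with 4.1.

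On the analysis, 7.2 plans to "evaluate potential differences in nasal/fecal microbiota composition during follow-up and in relation to different therapies administered". The Statistical analysis section relates microbiota at diagnosis, at follow-up points or at relapse to response, relapse-free survival and complications. Section 2.2 makes longitudinal sampling part of the secondary objectives.

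**The concern.** The schedules cannot all be followed, and nothing ranks them. A site working from 7.2 would collect different data from a site team working from 4.1 or 10.2.3, and a follow-up sample that was not taken cannot be recovered later, whatever an analysis plan says.

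The analysis most exposed is the one 7.2 itself announces. If a second sample exists only in patients who relapse, and is always taken at relapse before the next treatment line, then time since enrolment and relapse status cannot be separated. No sample would be scheduled during response or on treatment, and there would be no non-relapsing comparator over time. Under 4.1 the samples exist in everyone, but their number and timing vary with disease and clinical need. In addition, the section on consent describes a schedule that differs from the one in the procedures section, so patients may be told something other than what is done.

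**Working it through.** **Inputs**

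- Section 7.1: 40 AIHA, 40 ITP and 20 CIN patients a year; at least 200 patients; relapse risk of about 30% in AIHA and ITP; 40–50 patients expected to relapse in three years.
- Section 6: two years of enrolment; at least three years (36 months) of follow-up.
- Sections 4.1, 7.2 and 10.2.3: the schedules set out above.

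**Step 1. Reproduce the protocol's figures.**

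- N = 2 × (40 + 40 + 20) = 200, as stated.
- Relapsing patients = 0.30 × 2 × (40 + 40) = 0.30 × 160 = 48, inside the stated 40–50.

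**Step 2. Patients with only an enrolment sample if 7.2 is followed as written.** Formula: N − relapsing patients.

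| Relapsing patients | Enrolment sample only | Share of 200 |
|---|---|---|
| 40 | 160 | 80% |
| 48 | 152 | 76% |
| 50 | 150 | 75% |
| 60 (assumption: 30% also in CIN) | 140 | 70% |

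**Step 3. Planned sampling times per non-relapsing patient over 36 months.** Formula for 4.1: 1 + 36/visit interval in months.

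| Schedule | AIHA / ITP | CIN |
|---|---|---|
| 7.2 | 1 | 1 |
| 10.2.3 | 1 + 4 = 5 | 1 + 4 = 5 |
| 4.1 | 1 + 36/3 = 13 to 1 + 36/1 = 37 | 1 + 36/12 = 4 to 1 + 36/6 = 7 |

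**Step 4. Can the schedules be nested?**

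- *CIN.* In the first 12 months, 4.1 gives 1 + 12/12 = 2 to 1 + 12/6 = 3 sampling times, and 10.2.3 asks for 5. Months 1 and 3 fall before the first scheduled CIN visit.
- *AIHA and ITP.* Months 1, 3, 6 and 12 fall on monthly visits. On three-monthly visits, month 1 does not.
- *Relapse.* 4.1 and 7.2 require a sample; 10.2.3 lists none.
- *After month 12.* 4.1 continues for the remaining 24 of the 36 months; 10.2.3 stops; 7.2 continues only through relapse.

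No single reading satisfies all three sections.

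**Step 5. What remains analysable under 7.2 alone.** A paired enrolment-versus-relapse comparison in about 40–50 patients. A comparison of change over time between relapsers and non-relapsers does not remain, because the 150–160 non-relapsers have one time point each.

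**The case against.** The best defence is that 7.2 does not say its two occasions are the only ones. Read with its clause on new treatment lines, the sentence may fix pre-treatment timing at two key moments, and its own plan to look at follow-up presupposes follow-up samples. Sections 2.2, 4.1, 10.1 and the Statistical analysis section all provide for them. This has force. It means that the single-sample result is conditional on 7.2 being followed as written, and the protocol as a whole probably intends more. It does not remove the conflict: no section calls 7.2 a minimum, and even on that reading 10.2.3 still conflicts with the CIN visits and omits the relapse sample.

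It can also be said that the stakes are limited. Microbiota is not among the endpoints in section 5, its correlation with outcome is described as preliminary, and the study is descriptive. This stands and limits the weight of the point, but exploratory work still needs one schedule that can be carried out. Nor is this a matter to leave to an analysis plan, since it decides which samples exist.

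Two stronger readings are tempting.

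- A reader might infer that the follow-up comparison is impossible. It is not: the enrolment-versus-relapse comparison remains, though confounded.
- A reader might multiply out cohort totals, about 248 sample pairs under 7.2 (200 + 48) against up to 6,200 under 4.1 (160 × 37 + 40 × 7), and report a 25-fold gap. That sets extremes against each other. The upper figure has every AIHA and ITP patient sampled monthly for three years, although visits follow clinical need. The lower one includes relapse samples, at one per relapser, while the upper one leaves them out.

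**Conclusion.** The point holds as an internal inconsistency that should be corrected. Three sections set three sampling schedules, none is named as governing, and they cannot all be followed. Planned sampling times per non-relapsing patient over three years are 1, 5, and 13–37 (AIHA/ITP) or 4–7 (CIN), depending on the section used. If 7.2 is followed as written, 75–80% of 200 patients have an enrolment sample alone, and the follow-up and by-therapy analysis rests on 40–50 relapsers without a non-relapsing comparator.

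The figures assume 200 autoimmune cases, the protocol's own relapse expectation, and full three-year attendance. Patients enrolled under section 3.1 who turn out not to have an autoimmune cytopenia are not counted. The primary endpoint, the number of laboratory tests needed for diagnosis, is unaffected.

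A reader might also infer that patients have consented to the wrong schedule. The consent form is not at hand, so the documents show only that section 10.2.3 and section 4.1 disagree.

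**What to change.** Reconcile sections 4.1, 7.2, 10.1 and 10.2.3 into one research-sample schedule, stated identically or by cross-reference to one table. It should:

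- include follow-up samples in relapsers and non-relapsers alike;
- include a sample at relapse;
- be feasible for CIN patients within their visit intervals, or provide separate sampling contacts for them;
- match the schedule described to patients at consent.

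The choice of time points is the sponsor's. How samples taken at irregular times are modelled can be left to the analysis plan.

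The cost is one amendment, with a check of the consent text, and a total sample count that will be higher or lower than some sections now imply. It is best done early, because follow-up samples missed in the meantime cannot be collected afterwards.
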